**Planned exercise information**			
	Planned exercise activity; 9	Planning Questionnaire	What exercise do you plan to do on [day]? Please tell us the activity you plan to do; free text Please tell us roughly how long you plan to do your activity on [day]; free text
	Planned exercise intensity; 9	Planning Questionnaire	Please rate what you expect your overall level of exertion during your planned activity will be. This feeling should reflect how heavy and strenuous you expect the exercise to feel, combining all sensations and feelings of physical stress, effort, and fatigue. Focus on what you expect your total feeling of exertion will be, not any one specific factor?; 10-point scale ranging from 1=*rest* (no exertion at all) to 10=*maximal effort* (I was completely exhausted and it felt almost impossible to keep going)
**Exercise self-report information (after every planned exercise session)**			
	Exercise self-report; 18	Exercise self-report questionnaire	Did you do any exercise today?; Yes, No (conditional) Was the exercise you did today the same as what you originally planned, or different?; Exactly what I had planned; Different from what I had planned; I’m not sure, I can’t remember what I planned (conditional) What exercise did you do today?; free text (conditional) Please let us know why exercise didn’t fit into your day today (conditional) How did the exercise you did differ from what you had planned?; Pushed myself harder; Scaled back my activity; Did the activity in a different place or with different company; Did a different activity; Did the activity at a very different time than I had planned; Other difference
	Exercise exertion; 18	Exercise self-report questionnaire	Thinking back on your physical activity session today, rate your overall level of exertion during it. This feeling should reflect how heavy and strenuous the exercise felt to you, combining all sensations and feelings of physical stress, effort, and fatigue. Focus on your total feeling of exertion, not any one specific factor; 10-point scale ranging from 1=rest (no exertion at all) to 10=maximal effort (I was completely exhausted and it felt almost impossible to keep going)
	Affect during exercise (recollected); 18	Exercise self-report questionnaire	While you were doing your exercise session today, how did you feel overall?; free text Rate how good or bad you felt overall while you were doing your exercise; Feeling Scale [27]
	Postexercise affect (recollected); 18	Exercise self-report questionnaire	After you did your exercise session today, how did you feel overall?; free text Rate how good or bad you felt after your exercise session; Feeling Scale [27]
	Anticipated postexercise affect (next session); 19	Exercise self-report questionnaire and planning questionnaire (with baseline questions)	How do you expect to feel after your next exercise session? Select the number that best represents how good or bad you expect to feel; Feeling Scale [27]
	Unplanned exercise; 18	Exercise self-report questionnaire	Have you done any unplanned exercise since your last planned exercise session (not today’s)?; Yes, No, This was my first planned exercise session for this study (conditional) What was the unplanned exercise you did?; free text

^a^SRQ-E: Exercise Self-Regulation Questionnaire.

^b^PACES-8: Physical Activity Enjoyment Scale.

#### Study Procedures Overview

At enrollment, we will ask participants to write their low-reflection prompts and to self-report demographic and baseline activity–level information. In addition, we will assess participants’ anticipated affect for exercise, their affective association with exercise, and their overall enjoyment of exercise. On top of these measures, we will ask participants to complete the Exercise Self-Regulation Questionnaire [44,45] to measure their intrinsic motivation for exercise and the Physical Activity Enjoyment Scale (PACES-8) [46] to measure their enjoyment of exercise.

For the next 9 weeks, at the start of each week, participants will be asked to list 2 time intervals during which they plan to exercise in the coming week. At the start of each planned exercise time interval, participants will be randomized to receive an affective SMS text message (intervention), a control reminder message, or no message, and at the end of the day, they will be asked to report their actual exercise details (refer to *Exercise Data: Sensor and Self-Report Data* section). Thus, each participant will be randomized to receive an intervention, a control reminder message, or no message 2 times each week.

At the close of the 9-week period, participants will be sent a closing questionnaire that contains questions about their experience with the intervention, all items from the Exercise Self-Regulation Questionnaire and the PACES-8, and the same questions about affect related to exercise that were assessed at baseline.

After the 9-week study period, a subset of participants will be interviewed to gather in-depth data about their experience with the intervention and their perceptions of its impact on their attitudes toward exercise and on exercise behavior. We plan to stratify our interview sample based on participant characteristics such as exercise frequency and participant responses to the closing questionnaire, low-reflection sentences, and responses to high-reflection prompts.

#### Intervention Delivery

Microrandomized trials are designed around *decision points*—times when it may be appropriate and helpful to provide an intervention [42]. As the intervention in this study operates by increasing the salience of postexercise affective rewards, the intervention is likely to be most helpful when participants have an opportunity to exercise but have not yet exercised. To determine these times, participants will complete a planning questionnaire each weekend where they will specify 2 time intervals during which they intend to exercise in the coming week. Participants are asked to give a day and a 4-hour interval (eg, Thursday, 4-8 PM) during which they intend to exercise. We define an intervention decision point as the start of this interval (eg, Thursday, 4 PM). The 4-hour range was selected to be wide enough to give users some flexibility to accommodate small fluctuations in their schedules but narrow enough to still offer a targeted interval to measure outcomes without the addition of too many sources of noise. The planning questionnaire will be sent on Saturdays and again on Sundays and Monday evenings if not yet completed for the week. Participants who do not complete the questionnaire by the end of the day on Monday will not be sent any additional messages for the week.

The planning questionnaire will ask participants both when they intend to exercise and what exercise they plan to do. Participants can do any kind of exercise, as long as their session is at least 20 minutes long and is of moderate or greater intensity. Note that participants may exercise more frequently than twice a week, but only 2 of these sessions—those scheduled through the planning questionnaire—will determine the intervention decision points. Additional, unplanned exercise sessions will be assessed through sensor data and the exercise self-report questionnaire (refer to the *Exercise Data: Sensor and Self-Report Data* section).

The planning questionnaire will be delivered on a weekly, rather than daily, basis to minimize user burden and lower the risk of participant dropout. As the questionnaire requires participants to plan ahead, there is some chance that participants’ plans will change and that they will not exercise at their planned times. If participants change their plans for exercise after sending the planning questionnaire, the intervention may not reach them when they are truly receptive to it. However, the microrandomization of intervention delivery should balance this inaccuracy in delivery across conditions so that the observed effect of the intervention should not be biased in either direction, although it may be attenuated. In addition, the exercise self-report questionnaire, as well as Apple Watch data, will help in detecting whether participants actually exercised during their planned times (refer to *Exercise Data: Sensor and Self-Report Data* section).

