##### Randomization Procedure

As the number of decision points is known in advance (2 sessions/wk, or 18 decision points), we can construct randomized treatment sequences of length 18 for each of the 120 participants. These will be consistent with the 18 decision points per person. Before the start of the project, we created 120 randomization schedules to account for the required sample size, allowing for dropouts. Each schedule consists of a sequence of 18 numbers. To ensure that we achieved the right condition balance across participants, we drew these numbers randomly from a uniform number distribution, then placed them randomly into a hundred 18-number sequences. From the numbers that were randomly selected, we assigned the bottom 30% to the control condition, the next 30% to the reminder condition, and the top 40% to the high- or low-reflection affective message conditions. The result is a randomized sequence of condition assignments for the duration of the study, independent of the time and date of planned exercise sessions (refer to Multimedia Appendix 1 for an example randomization schedule). Across all randomization schedules but not within schedules, the conditions are balanced such that 30% of the planned exercise sessions are assigned to control, 30% to the reminder message condition, and 40% to an affective message condition. We then carried out a second round of randomization on the affective message condition sessions to determine which messages would be sent (eg, high-reflection message 1 and low-reflection message 2). As participants will create a set number of low-reflection messages based on fill-in-the-blank templates, we can randomize message selection before message creation. When a participant enrolls, they will be assigned to a randomization schedule. The actual time and date at which each message is sent will be based on the participants’ responses to the planning questionnaires each week.

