#### Primary Outcome

The primary outcome for the microrandomized trial will be *calories burned*, as assessed by the Apple Watch, over the planned 4-hour exercise periods scheduled through the planning questionnaire. Apple Watch data will be collected through the MyDataHelps platform (CareEvolution, LLC), a secure platform for the collection of sensor (Apple Watch and Fitbit) and self-report data in health research. Participants will install the MyDataHelps app on their mobile phone. As calories burned can be reported by Apple Watch in discontinuous intervals, we will sum the calories burned over the 4-hour planned exercise period. When the intervals of reported calorie data cross the 4-hour planned exercise period boundary, we will assume that the calories burned are equally distributed across the reported interval and include only these calories in the 4-hour planned exercise period. Although Apple Watch’s calories burned measurement has moderate rather than high correlation with other energy expenditure measures [52], calories burned were selected as the primary outcome measure because it enables us to assess participants’ engagement in a greater variety of exercises compared with a more restrictive measure, such as steps. In this study, participants are instructed to perform any moderate to vigorous exercise they choose and to tell us what they plan to do in the planning questionnaire. Other data (described in the next subsection) will provide secondary records of the exercise performed for secondary analyses.

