#### Exercise Data: Sensor and Self-Report Data

In addition to exercise being assessed via calories burned, it will also be assessed through several additional Apple Watch metrics, including active minutes, steps, and standing time. These metrics will also be collected through the MyDataHelps mobile app. As with calories burned, we will analyze step data and active minutes in the 4-hour planned exercise period.

On the days that participants plan to exercise, they will be asked to complete an exercise self-report questionnaire in the evening asking whether they exercised that day and, if so, how their activity compared with what they had planned; for example, was it shorter or longer in duration than they had planned? Participants will further be asked about their perceived exertion and affective state during and after exercise and, as a manipulation check, whether they received and read an SMS text message from the study team before exercise. If participants say they did not exercise, they will be asked why.

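### Watch activity earlier on the same day is collected but not named as a covariate or moderator, so the plan forgoes possible precision and never examines the effect in participants who have not yet exercised

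*Protocol article*

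**What the plan says.** All places are in the protocol article.

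- **Intervention Delivery** gives the rationale for timing: "the intervention is likely to be most helpful when participants have an opportunity to exercise but have not yet exercised". These times are set by a questionnaire completed at the weekend, and the decision point is the start of the 4-hour interval the participant chose. Participants may exercise more than twice a week, and "Additional, unplanned exercise sessions will be assessed through sensor data and the exercise self-report questionnaire".
- **Randomization Procedure**: schedules were drawn up in advance. "The result is a randomized sequence of condition assignments for the duration of the study, independent of the time and date of planned exercise sessions".
- **Primary Outcome**: "we will sum the calories burned over the 4-hour planned exercise period". The section on sensor and self-report data applies the same limit to the other watch outcomes: "we will analyze step data and active minutes in the 4-hour planned exercise period".
- **Primary Analysis** lists as covariates time in study, the previous week's proximal outcome, self-reported baseline activity, age and gender.
- **Secondary and Exploratory Analyses** names baseline activity level, planned intensity and exercise intensity as possible moderators, in connection with predictions of postexercise affect.
- **Sample Size and Power**: effect 0.2, significance .05, power 0.9, and availability 0.7 solely to take out reminder occasions. This gives 89 participants, with up to 120 to be recruited.
- **Intervention Delivery** and **Implications and Limitations** both accept that changed plans can mistime a message. They argue that randomization balances this, so the effect is unbiased but may be attenuated.

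**The concern.** The protocol names a state in which the message should work best, and it collects a sensor stream that can show whether the participant was in that state when the window opened. The analysis as described does not use that reading. A decision point that follows a morning run enters the model in the same way as one on a day with no exercise so far.

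Two things are at stake. First, activity earlier in the day may predict calories inside the window. If it does, leaving it out gives a wider interval than the data allow. Second, if the message does little once exercise is done, the average effect is diluted, and the study will not show whether a weak average reflects a weak message or a badly timed one. If that split is chosen only after results are seen, it will carry little weight.

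**Working it through.** **1. Is the reading available, and is it valid to use?** Unplanned sessions are to be assessed by sensor, so the watch stream is not confined to the planned windows. Activity recorded before a window opens precedes that window's message, and the assignment was generated in advance. Using it as a control covariate or moderator in the weighted and centered least squares analysis therefore leaves the randomized comparison intact.

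The checks the article does offer differ in this respect. Whether the participant exercised during the planned time is known only after the message. The evening questionnaire also comes after it, and its option "Did the activity at a very different time than I had planned" does not say whether the activity came before or after the window. Sorting decision points by such variables could break the comparison.

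**2. Reproducing the plan's 89.** Inputs: T = 18 decision points, availability τ = 0.7, effect d = 0.2, α = 0.05, constant effect. The test is a noncentral F with 1 numerator degree of freedom and noncentrality λ = N·T·τ·ρ(1 − ρ)·d².

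- ρ = 0.4: λ = 89 × 18 × 0.7 × 0.24 × 0.04 = 10.77. The smallest N for 90% power is 89, as stated.
- ρ = 0.4/0.7 = 0.571 (the share within the primary contrast): λ = 89 × 18 × 0.7 × 0.2449 × 0.04 = 10.99. Power at 89 is 90.6%, and the smallest N is 88.

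**3. Dilution, as an illustration.** Assume that a share f of decision points follows exercise, that the effect there is zero, and that outcome variance is unchanged. The article gives no value for f. The average effect becomes 0.2(1 − f).

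Normal approximation, starting from 1.960 + 1.282 = 3.242:
- f = 10%: Φ(3.242 × 0.9 − 1.96) = Φ(0.958) = 0.83
- f = 20%: Φ(3.242 × 0.8 − 1.96) = Φ(0.634) = 0.74

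Noncentral F with ρ = 0.571:

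| f | Average effect | Power at 89, all points | Power at 120, all points | Power at 89, not-yet-exercised points only |
|---|---|---|---|---|
| 0 | 0.20 | 90.6% | 96.8% | 90.6% |
| 5% | 0.19 | 87.6% | 95.2% | 89.2% |
| 10% | 0.18 | 83.9% | 93.0% | 87.5% |
| 20% | 0.16 | 74.6% | 86.3% | 83.4% |
| 30% | 0.14 | 63.1% | 76.2% | 78.3% |

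The last column keeps d = 0.2 and sets availability to 0.7(1 − f). The column for 120 supposes that nobody drops out.

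**4. Precision from a covariate.** With residual correlation r between pre-window activity and the outcome, the variance factor is 1 − r². For an assumed r of 0.2 it is 1 − 0.04 = 0.96, and for 0.5 it is 1 − 0.25 = 0.75. In sample-size terms (ρ = 0.571), explaining an assumed 5% to 30% of residual variance would lower the N for 90% power from 88 to between 83 and 62. This gain does not depend on f.

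**5. What each remedy recovers.** The covariate acts only through step 4: the average effect over all decision points stays at 0.2(1 − f). Only a moderated estimate speaks to the not-yet-exercised state, and it answers a secondary question.

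**The case against.** The strongest reply is that nothing here is wrong as written. The timing sentence is a rationale, put into practice through the weekend questionnaire, and can be read simply as meaning before the planned session. The stated target is the average effect over planned periods, so imperfect moments belong to it. Attenuation is disclosed twice and defended as realistic. The covariate list is not declared exhaustive, the moderators are given as examples, and an analysis plan that is not shown may add more. The power figures assume the extreme case of no effect after exercise, although an earlier walk need not cancel an evening session, and they are set at 89 rather than 120. Finally, cumulative same-day calories partly measure the time of day, and the model already holds the previous week's outcome and baseline activity, so a residual correlation as high as 0.5 has no support in the text.

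Most of this stands. It rules out any claim of error in the estimand or the sample size, and it means the covariate must be built with care. It does not remove the point. The article does state a covariate list and does confine the watch outcomes to the window. It adjusts for activity a week old but names no same-day reading that also precedes the message. The disclosed limitation concerns changed plans, and the checks offered for it are recorded after the message.

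**Conclusion.** The point holds as a low-cost improvement to a stated method. The article names no use of same-day activity before the message, although the watch can supply it and the protocol's own rationale makes it relevant. The consequences are possible loss of precision and an unexamined effect in the state the protocol names.

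A reader might infer more, and the documents do not support it:

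- *That the primary estimate is biased.* It is not. Assignment is pre-generated and independent of earlier activity.
- *That the protocol contradicts itself, or restricts the message to people who have not exercised.* It calls such moments likely to be the most helpful and sets no availability rule.
- *That the watch records nothing before the message.* Sensor assessment of unplanned sessions implies that it does.
- *That the trial is underpowered.* The 89 reproduces. The 83% and 74% hold only for 89 participants with an assumed 10% or 20% of already-exercised points and zero effect at those points.

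The share f, the zero effect and r are all assumptions. The article fixes none of them, so the actual loss is unknown.

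**What to change.** 1. Keep the primary estimand over all decision points.
2. Derive same-day watch activity before each window opens, as a rate or over a fixed look-back so that it does not merely reflect when the window starts. Add it to the primary model as a control covariate, together with time of day and a missing-data indicator so that no decision point is dropped.
3. Prespecify, as a secondary analysis, the message effect moderated by whether an exercise bout of at least 20 active minutes was recorded earlier that day. Twenty minutes is the study's own minimum session length.
4. State that the covariate is there for precision and does not remove dilution from the primary effect.

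The cost is a few lines of analysis text and a few variables derived from data already collected. The limits should be stated: values are missing when the watch was off, early windows have little pre-window data, and the bout flag may catch routine walking. The additions should be fixed before outcome data are examined, because a split chosen afterwards would not be credible.

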#### Reminder Message

The planning questionnaire enables the delivery of the affective intervention messages, but, as a form of implementation intention, it could influence behavior in its own right [48,49]. Specifically, the affective messages may work as reminders of previously made plans, which have been shown to improve the effectiveness of planning [50,51]. We control for these effects by including a reminder message whose delivery will be randomized along with that of the affective intervention messages. The reminder message simply reminds participants to fill out the exercise day questionnaire. As in the case of the affective intervention messages, reminder messages will be sent at the start of the planned exercise interval.

#### Randomization During the 9-Week Trial

##### Randomization Overview

For each planned exercise interval, participants will be randomly assigned to receive an affective intervention message (40% probability), a reminder message (30% probability), or no message (30% probability; Figure 1). If participants are randomized to receive an affective intervention message, they will be further randomly assigned to receive either a high-reflection message or a low-reflection message with equal probability (ie, 20% each). For each participant, as there will be 9 high-reflection messages and 9 low-reflection messages to choose from, the message to be sent will be chosen from the appropriate set randomly without replacement so that participants will not receive the same message twice.

##### Randomization Procedure

As the number of decision points is known in advance (2 sessions/wk, or 18 decision points), we can construct randomized treatment sequences of length 18 for each of the 120 participants. These will be consistent with the 18 decision points per person. Before the start of the project, we created 120 randomization schedules to account for the required sample size, allowing for dropouts. Each schedule consists of a sequence of 18 numbers. To ensure that we achieved the right condition balance across participants, we drew these numbers randomly from a uniform number distribution, then placed them randomly into a hundred 18-number sequences. From the numbers that were randomly selected, we assigned the bottom 30% to the control condition, the next 30% to the reminder condition, and the top 40% to the high- or low-reflection affective message conditions. The result is a randomized sequence of condition assignments for the duration of the study, independent of the time and date of planned exercise sessions (refer to Multimedia Appendix 1 for an example randomization schedule). Across all randomization schedules but not within schedules, the conditions are balanced such that 30% of the planned exercise sessions are assigned to control, 30% to the reminder message condition, and 40% to an affective message condition. We then carried out a second round of randomization on the affective message condition sessions to determine which messages would be sent (eg, high-reflection message 1 and low-reflection message 2). As participants will create a set number of low-reflection messages based on fill-in-the-blank templates, we can randomize message selection before message creation. When a participant enrolls, they will be assigned to a randomization schedule. The actual time and date at which each message is sent will be based on the participants’ responses to the planning questionnaires each week.

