### Sample Size and Power

Sample size was calculated according to the methods published by Liao et al [43]. A microrandomized trial is an efficient trial design that enables causal inference with relatively small samples [42,43]. For this study, proximal treatment effect was estimated at 0.2, significance set at .05, and power set to 0.9. To power our study for the primary analysis (refer to the next subsection)—a contrast between no message and affective messages—availability was set to 0.7 to exclude reminder messages that are randomized at 30% probability. Given these assumptions, 89 participants are needed. We intend to recruit up to 120, allowing for dropouts.

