### Data Analyses

#### Primary Analysis

Our primary interest is the average effect of the affective message intervention across time on calories burned during the planned exercise periods compared with no message being sent. To assess this effect, we will use the centered and weighted least squares method, a standard approach for analyzing microrandomized trial data that allows for robust causal inferences about treatment effects [53] and accounts for correlations in longitudinal data by nesting outcomes within participants. The covariates in our analysis will include time in study, the prior week’s proximal outcome, self-reported baseline activity levels, age, and gender.

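### Optional precision gain: the primary model uses only the prior week of each participant's watch history, although all earlier planned windows could serve as covariates

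*Protocol article*

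**What the plan says.** All references are to the protocol article.

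- **Randomization Procedure:** each participant has a sequence of 18 assignments. The 30/30/40 split is fixed over the whole set of schedules only: "Across all randomization schedules but not within schedules, the conditions are balanced".
- **Primary Analysis:** the covariates are time in study, the prior week's proximal outcome, and "self-reported baseline activity levels, age, and gender". The centered and weighted least squares method is said to be one that "accounts for correlations in longitudinal data by nesting outcomes within participants".
- **Sample Size and Power:** "proximal treatment effect was estimated at 0.2, significance set at .05, and power set to 0.9", and "availability was set to 0.7 to exclude reminder messages that are randomized at 30% probability". The result: "Given these assumptions, 89 participants are needed. We intend to recruit up to 120, allowing for dropouts".
- **Intervention Delivery:** participants plan two 4-hour windows a week, so the prior week supplies at most two outcome values.

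**The concern.** People differ persistently in the calories they burn in a 4-hour window. Because assignments are not balanced within a participant, some people contribute mostly affective sessions and others mostly no-message sessions, so part of the stable difference between people enters the error of the primary contrast. Clustering by participant gives a correct standard error for this but does not remove the variance. Only covariates do that.

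The listed covariates remove some of it. Baseline activity, however, is a single self-reported item on exercise days per week, and the only watch-based information about a person's level is the prior week. By the middle of the study eight earlier planned windows may exist, and at most two are used.

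What is at stake is the width of the confidence interval for an effect assumed to be small (0.2). The validity of the estimate is not in question.

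**Working it through.** **1. The stated sample size.** The usual F-test formula for a constant effect in a microrandomized trial has noncentrality N × 18 × 0.7 × p(1−p) × 0.2², with 1 and N−2 degrees of freedom. The article does not state which p was used.
- p = 0.4: 89 × 18 × 0.7 × 0.24 × 0.04 = 10.77, power 0.9005. N = 88 gives 0.897, so 89 is the smallest N.
- p = 4/7 (affective share once reminders are excluded): noncentrality 10.99 at N = 89, power 0.906. N = 88 suffices.

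The 89 reproduces. The formula takes out no between-person variance, so if 0.2 is in units of the total SD, the stable differences are already paid for. Simulated power at N = 89 with no person-level covariates was 0.90 to 0.91 at ICC 0.3, 0.5 and 0.7. With the prior week added it was 0.97 at ICC 0.5. If 0.2 is in units of the residual SD, 88 to 89 holds by definition.

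**2. Chance imbalance within a participant.** The number of affective sessions has mean 18 × 0.4 = 7.2 and SD √(18 × 0.4 × 0.6) = 2.08. The probability of two or fewer no-message sessions out of 18 is 0.060 (binomial, 0.3).

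**3. What the prior week removes.** Assume equal correlation between a person's sessions and total variance 1. The residual variance after adjusting for the mean of k earlier windows is r(k) = 1 − k·ICC² / (1 + (k−1)·ICC). With k = 2, the share of between-person variance left is (1−ICC)/(1+ICC).

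| ICC (assumed) | Share left after prior week | r(2) | r(8), start of week 5 | r(16), start of week 9 |
|---|---|---|---|---|
| 0.2 | 0.8/1.2 = 67% | 0.933 | 0.867 | 0.840 |
| 0.4 | 0.6/1.4 = 43% | 0.771 | 0.663 | 0.634 |
| 0.6 | 0.4/1.6 = 25% | 0.550 | 0.446 | 0.424 |

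The prior week alone thus removes about 33%, 57% and 75% of the between-person variance. Baseline activity, age and gender remove some more.

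**4. What the longer history adds.** With independently drawn, centered assignments, the variance of the estimate is proportional to the average residual variance.
- Prior week only: the two sessions of week 1 have no history, so the average is (2 × 1 + 16 × r(2))/18 = 0.941, 0.797 and 0.600.
- All earlier windows: averaging r(0) to r(17), with r(0) = 1, gives 0.881, 0.697 and 0.494.
- Ratios: 0.94, 0.87 and 0.82, that is 6%, 13% and 18% less variance.

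**5. Simulation under less ideal conditions.** Settings: 100 participants, 15% of weeks unplanned, baseline covariates explaining 15% of between-person variance, an indicator for a missing prior-week value, reminder sessions excluded, true effect 0.2, and errors either exchangeable or with added AR(1) correlation of 0.3. The ratio of variances (history model to listed model) was 0.94-0.96 at ICC 0.2, 0.87-0.90 at 0.4 and 0.75-0.82 at 0.6, over runs that coded the history slightly differently. Mean estimates were 0.198 to 0.204, so no bias appeared. Weighting the mean further by the number of earlier windows added almost nothing.

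**6. Validity.** Under the planned randomization at N = 89, bias was about zero with or without covariates. Type I error was 0.046 to 0.065, with no trend by ICC.

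**The case against.** The strongest case against is that nothing here is wrong. The estimator is unbiased, the standard error is right, and almost any parsimonious model could be made more precise. The prior week's outcome is a simple, defensible covariate and already does much of the work. The gain rests on an ICC that the documents do not give; at 0.2 it is about 5% of the variance, or 2-3% of the standard error (√0.96 = 0.98, √0.94 = 0.97). The covariate list is not worded as exhaustive, and how outcome history is summarized may be settled in an analysis plan that is not shown.

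Most of this stands. It makes the point an optional improvement, and if the full plan already uses the longer history, nothing needs to change. What remains is that the article names its history covariate, and that choice leaves usable information aside.

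A reader might infer more, but the documents do not support it:
- **That the randomization is faulty.** Assignment without forced balance within a person suits the analysis method. In simulation, forcing balance while keeping the lagged outcome in the model produced a small bias (+0.004 to +0.009 at an effect of 0.2).
- **That the model holds only the prior week's outcome.** It also lists time in study, baseline activity, age and gender.
- **That the trial is underpowered or its test invalid.** The 89 reproduces, power does not rest on removing this variance, and type I error is unaffected.

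**Conclusion.** The point holds as a cheap gain in precision and nothing more. The part of stable between-person variation that the listed covariates miss stays in the error of the primary contrast, and the participant's earlier planned windows could remove more of it.

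The variance of the primary estimate would fall by roughly 4-6%, 11-13% and 18-25% at assumed ICCs of 0.2, 0.4 and 0.6; one run at ICC 0.4 gave 10%. In participants, this is worth from 1/0.96 − 1 = 4% to 1/0.75 − 1 = 33% more enrollment, and 12-15% at ICC 0.4 (1/0.89 and 1/0.87).

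These sizes depend on the assumed ICC, the error structure, the share of unplanned weeks and what the baseline covariates explain. None of these is given in the documents. The upper end needs a high ICC, for which they offer no evidence.

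**What to change.** Before the data are analyzed, keep the listed covariates of the primary model and add two terms:
- the participant's mean calories over all planned windows before the decision point, whatever was assigned in them;
- an indicator for no earlier window, with the mean set to a constant there.

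Keep participant-clustered standard errors. Use the matching history means in the secondary models for step count and active minutes. Leave the randomization schedules as they are.

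The cost is two derived variables per outcome, two extra model terms and one sentence in the analysis section. No new data, participant burden or enrollment is needed. Fixing it in advance matters because covariates chosen after seeing results would invite doubt.
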